**b. Foreskin**

Immediately upon arrival in the laboratory, foreskin tissue will be cut and divided into sections to investigate *ex vivo* challenge, pharmacokinetics, inflammation and microbiome.

**c. Urethral swab**

Samples will be transported to the University of Cape Town after 50% recruitment and at the end of the study. These samples will be analysed for markers of inflammation.

**d. Corona sulcus swab**

Samples will be transported to the University of Cape town after 50% recruitment and at the end of the study. These samples will be sequenced, and microbiome species quantified.

**e. Rectal swab**

Samples will be transported to the University of Liverpool after 50% recruitment and at the end of the study. These samples will have drug levels measured.

**f. Urine sample**

Mid-stream urine samples (5ml) will be transported to the University of Liverpool after 50% recruitment and at the end of the study. These samples will have drug levels measured.

## **7.4 End point Sample Analysis**

**a. Ex vivo challenge of foreskin tissue and PBMCs**

Quantification of protection from HIV-1 infection in foreskin tissue and PBMCs will be initially carried out in local laboratories. In brief, foreskin explants will be challenged or not (for negative background control tests) *ex vivo* with HIV-1BaL at two titers; a high titer normally used in pre-clinical assays in the laboratory and a low titer trying to mimic *in vivo* levels. *Ex vivo* challenge will be performed using a non-polarized system by submerging the tissue explant in 200 µl of

virus diluted at the appropriate titer. Following 2 h of incubation, explants will be washed with PBS to remove unbound virus and transferred to a fresh culture plate. Tissue explants will then be cultured for 15 days and maintained by harvesting approximately two-thirds of culture supernatant at days 3, 7, 11 and 15, and refeeding the cultures with fresh medium. The extent of virus replication in tissue explants will be determined by measuring the p24 antigen concentration for HIV-1 in supernatants at each harvest time point with antigen-specific ELISA. The supernatant fluid collected from the culture supernatants will be stored and subsequently analysed for HIV infection at Imperial College London. Interim analyses after 30% and 60% recruitment will confirm continued validation of assays and whether recruitment needs to be extended in any arm.

*Ex vivo* dosing of foreskin explants with FTC-TDF or FTC-TAF will be used to i) mimic the postcoitus dosing in the IPERGAY trial; and ii) evaluate the time frame for initiating PEP with FTC- TDF or FTC-TAF. In the first case, to mimic IPERGAY, foreskin samples obtained from CHAPS participant who will have received one or two pills of FTC-TDF or FTC-TAF, will be dosed by submerging the explant in 200ul of drug diluted at the appropriate concentration, 18hrs after *ex vivo* viral challenge.

To pre-clinically evaluate the potential of FTC-TDF and FTC-TAF as PEP drugs and determine the maximum time after HIV exposure that PEP can be initiated effectively, we will use foreskin specimens from participants in the control arm of CHAPS who will not have taken FTC-TDF nor FTC-TAF prior to circumcision. Foreskin explants will be dosed in a non-polarized manner as described above either 1 h, 24h, 48 h or 72 h post-viral *ex vivo* challenge. During *in vivo* dosing, formulations contain drug levels in excess of the known *in vitro* inhibitory concentration. Hence, for both objectives [i) and ii)], a fully *ex vivo* inhibitory dose of drug (1 mg/ml) will be used.

**b. Drug level measurement**

Concentrations of FTC, TFV and TAF, including intracellular triphosphates (TFV-DP, FTC-TP) will be measured in the plasma, urine, rectal secretions and foreskin (tissue homogenate as well as isolated CD4+ cells from the foreskin) of volunteers, as shown in Table 3, at the Liverpool GCP Bioanalytical Facility, UK, UK. PBMCs and CD4+ expressing cells isolated from whole blood will be stored for further determination of intracellular TFV-DP/FTC-TP which is not included in the costs of the study.

**c. Microbiome**

The University of Cape Town will determine the microbiome of skin the penis, using sterile moistened HydroFlock® swabs. The microbiome will be analysed using 16S rRNA sequencing to identify the diversity, relative and differential abundance of microbes of the coronal sulcus.

**d. Cytokines:**

An array of cytokines/chemokines will be measured using an in house Luminex multi-bead array designed by Imperial College and use culture supernatants derived from the PBMC and foreskin tissue which have been exposed to HIV using ex vivo challenge.

**e. Gene expression**

The Karolinska Institute will analyse genes that are involved in inflammation processes in foreskin tissue and which may be potentially affected by treatment. The analyses will be conducted with commercially available microarrays which assemble genes related to inflammation.

**f. Immune cells in foreskin tissue**

The UCT will analyse cut blocks of tissue using a combination of immunohistochemistry immunofluorescence microscopy for the numbers of activated HIV target cells (Langerhan's cells, CD4+CCR5+ T cells and dendritic cells) and their location in the inner and outer foreskin. The analysis will be performed on a subset of foreskin tissues from trial participants who show either no ex-vivo protection or >75% ex vivo protection.

**g. Proteomics**

UCT will analyse stored foreskin tissue for targeted tight junction proteins as a measure of tissue and barrier integrity

**Table 3: Sample collection and sample analysis**

| Specimen type | Volume/amount of sample | analysis                                             |
|----------------------|--------------------------------|-------------------------------------------------------------|
| Safety blood         | 4ml EDTA
5ml SSAT           | Haemoglobin
HIV                                          |
| Research blood       | 51mls ACD                      | Ex vivo challenge, drug levels, cytokines                   |
| Rectal swab          | 1 swab                         | Drug levels                                                 |
| Urethral swab        | 1 swab                         | Inflammation                                                |
| Coronal sulcus swab  | 1 swab                         | Microbiome                                                  |
| Foreskin             | Circumcised foreskin           | ex vivo challenge, drug levels, inflammation and microbiome |
| Urine                | 5ml
5ml                     | Drug level
STI screen                                    |

**Table 4: Drug levels to be measured at VMMC visit**

|                                   | Parent drug:
TAF/TFV/FTC | Metabolite:
TFV-DP/FTC-TP |
|-----------------------------------|-------------------------------------|--------------------------------------|
| Blood:                            |                                     |                                      |
| - Plasma *                        | X                                   |                                      |
| - CD4+ expressing cells in PBMC * |                                     | X                                    |
| Urine*                            | X                                   |                                      |
| Rectal fluid (optional)*          | X                                   |                                      |
| Foreskin:                         |                                     |                                      |
| - CD4 expressing cells            |                                     | X                                    |
| - non CD4+ population             |                                     | X                                    |
| - Total tissue homogenate         | X                                   | X                                    |

\*Blood, urine and rectal samples must be taken 0 to 40 mins prior to VMMC

## **8. Assessment of Safety**

### **8.1 Specification, Timing and Recording of Safety Parameters**

Participant safety will be determined by physical examination, blood tests and adverse event reporting.

## **8.2 Management of potential adverse outcomes after VMMC**

Study participants will be given the locally approved routine information regarding which symptoms should alert them to the possibility of infection or a major bleed following their VMMC. In the event of these symptoms they will be advised to attend their local Hospital and to take with them their VMMC Patient Information sheet and inform the medical staff that they have recently undergone VMMC.

## **8.3 Management of HIV-1 diagnosis**

Volunteers who are found to be HIV-1 infected at screening will be provided with HIV counselling and referred to HIV care according to local guidelines.

## **8.4 Procedures for Recording and Reporting Adverse Events**

### **Adverse Events**

An AE is defined as any untoward medical occurrence (including an abnormal laboratory finding) in a clinical research participant which may or may not have a causal relationship with the study product. Study product refers to TDF and FTAF. Recording of AEs for this study beginning from the time of randomisation.

### **Adverse Event Reporting**

Symptoms or conditions that occur prior to randomisation will be recorded in the participant's medical history as pre-existing conditions. All new or worsening symptoms or conditions that occur following randomisation will be considered AEs and will be recorded on the AE CRF regardless of severity and relationship to study product. AEs that are ongoing at the time of study exit will be followed up for up to 30 days after study exit and then, if not resolved, will

be referred to a health care provider for further follow-up. After this period sites must report serious, unexpected, clinical suspected adverse drug reactions if the study site becomes aware of the event on a passive basis, i.e., from publicly available information.

Study staff will document in source documents and the appropriate CRF AEs reported by or observed in enrolled study participants regardless of severity and presumed relationship to study product. Relatedness is an assessment made by a study clinician of whether or not the event is related to the

study agent. The relationship of all AEs to study product will be assessed as either related or not related.

AE severity will be graded according to the grading table. (eg. DAIDS grading table) This version will be used for the entire duration of the study. For this study, all Grade 3 or above events or reactions will be reported as adverse events.

Sites may be required to submit AE and SAE information to local regulatory agencies or other local authorities per in country guidelines.

Study participants will be provided with contact telephone numbers to report any AEs they may experience, except for life-threatening events, for which they will be instructed to seek immediate emergency care.

### **Serious Adverse Event (SAE) Reporting**

An SAE includes any experience that is:

- fatal or life-threatening,
- results in persistent or significant disability/incapacity,
- requires or prolongs hospitalization,
- is a congenital anomaly, or is an important medical event that, based upon medical judgment, may jeopardize the participant and may require intervention to prevent one of the previous four outcomes listed above.

A life-threatening AE means that the participant was, in the view of the designated study staff, at immediate risk of death from the condition as it occurred. Notification of deaths will be

recorded by reflecting the medical condition that led to the death on the AE CRF and also reported on the SAE report

Reporting SAEs may require additional reports and follow-up, depending upon the study clinician's assessment of a causal relationship between the study product and the AE(s), and whether the AE(s) is identified in nature, severity, and frequency in the Investigator's Brochure or other risk information supplied to the Investigator.

## **8.5 Treatment Stopping Rules**

The trial may be prematurely discontinued by the Sponsor, Chief Investigator, ethics committee or

Regulatory Authority based on new safety information. If the study is prematurely discontinued, active participants will be informed and no further participant data will be collected.

We do not expect any serious adverse events from ARV received during the study- participants receive a maximum of three doses of PrEP only. However, if a participant experiences side effects the drug can be withdrawn at any time. If the drug is stopped prematurely then the participant will be withdrawn from the study and replaced.

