### **7.1.5 Exit safety visit after VMMC**

- Physical / genital exam if clinically indicated
- Concomitant medications review
- AE review. If adverse events have been reported, these will be clinically followed in accordance to the instruction of the study physician.

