## **10. Criteria for termination of the trial**

The Sponsor or Investigator may terminate either part of, or the entire trial for safety or administrative reasons. A written statement fully documenting the reasons for such a termination will be provided to the Ethics Committee and the Regulatory Authorities as appropriate.

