## **13. Independent Data Monitoring Committee (IDMC)**

An Independent Data Monitoring Committee (IDMC) will be formed. The IDMC will be the only group which sees the confidential, accumulating data for the study separately by randomised group. The IDMC will review study data on recruitment, safety, adherence to randomised strategies and efficacy, as well as consider findings from any other relevant studies. The IDMC will meet after the first 10 participants have completed the study the frequency of meetings will be dictated in the IDMC charter. The IDMC will consider data using the statistical analysis plan and will advise the TSC. The IDMC can recommend premature stopping, reporting or modification.

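### Section 8.5 stops all participant data collection after an early stop with no safety exception; taken literally, it cancels the exit AE review and new AE recording for men already dosed or circumcised

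*Protocol*

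**What the plan says.** Protocol section 8.5 (Treatment Stopping Rules) names those who may stop the trial early and gives new information on safety as the ground. The next sentence reads: "If the study is prematurely discontinued, active participants will be informed and no further participant data will be collected". It is not limited to research or endpoint data.

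Other sections ask for safety data from the same men:

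- Section 8.4, Adverse Event Reporting: "All new or worsening symptoms or conditions that occur following randomisation will be considered AEs and will be recorded on the AE CRF", whatever the severity or relationship to the drug.
- The same section: "AEs that are ongoing at the time of study exit will be followed up for up to 30 days after study exit". After that period, sites still report serious unexpected suspected reactions that they learn of passively.
- Section 8.4, Serious Adverse Event (SAE) Reporting: "Reporting SAEs may require additional reports and follow-up".
- Section 7.1.5, exit safety visit: "AE review. If adverse events have been reported, these will be clinically followed in accordance to the instruction of the study physician".

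Section 10 is the other text on stopping: "The Sponsor or Investigator may terminate either part of, or the entire trial for safety or administrative reasons". It adds only a written statement of reasons to the ethics committee and regulators.

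**The concern.** The rule in section 8.5 applies in the situation where safety data on exposed men are most wanted. Someone has judged that safety information justifies closing the trial, and the same paragraph then ends collection from men who have just taken the drug or just had surgery. The information may come from inside the trial or from elsewhere; section 13 has the IDMC review trial data "as well as consider findings from any other relevant studies". Either way, a site that follows section 8.5 to the letter would not record an event that first appears after the stop in a man still awaiting his exit visit. Two sites in two countries would have to decide, during a safety closure, which section prevails.

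At stake is the completeness of the safety record for a few men. No sample size or error rate depends on it.

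**Working it through.** The protocol gives no figure for this, so there is none to reproduce. The check has two parts.

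**1. The texts side by side, for a man dosed or circumcised before the stop**

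| Duty | Section | Under a literal 8.5 |
|---|---|---|
| AE review at the exit visit | 7.1.5 | Cancelled; nothing restores it |
| New AEs entered on the CRF | 8.4 | Cancelled; nothing restores it |
| Up to 30 days' follow-up of AEs ongoing at exit | 8.4 | Unclear; survives if the stop counts as study exit |
| Further SAE reports and follow-up | 8.4 | Conditional wording; only a weak conflict |
| AEs recorded up to the stop | 7.1.3, 7.1.4, 8.4 | Kept; 8.5 bars only further collection |
| Advice and access to care | 8.2, 8.4 | Unaffected |

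Sections 10 (termination), 13 (IDMC) and 15 (ethics and regulatory approvals) contain no rule on safety follow-up after closure. Section 6.5 deals with individual withdrawal, not closure of the trial.

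**2. How many men are in the gap at any one time**

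Formula: men in the interval = accrual per day × length of the interval in days.

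Inputs:

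- Duration 12 months (section 6.6), taken as 365 days. Uniform accrual is assumed.
- 144 men, giving 144/365 = 0.395 per day. As an upper bound, 200 men: section 4.2 allows a maximum of 100 randomised to obtain 72 evaluable, and since 72 is the per-country number I read 100 as per country. Then 200/365 = 0.548 per day.
- Gap from circumcision to exit visit. This is not fixed, because section 7.1.2 lets surgery fall up to 21 days after randomisation. The assumed low value is 3 days (Table 3.5: surgery on Day 3, exit window opening on Day 6). The high value is 21 days, if the Day 21 limit is counted from surgery. The middle value is 14 days.

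Circumcised and awaiting exit:

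- Low: 0.395 × 3 = 1.2
- Middle: 0.395 × 14 = 5.5
- High: 0.548 × 21 = 11.5

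Dosed but not yet circumcised: first dose to surgery takes 5, 21, 24 + 5 = 29, or 24 + 21 = 45 hours (Table 1). The mean is 100/4 = 25 hours = 1.04 days, in 8 of 9 arms.

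- 0.395 × (8/9) × 1.04 = 0.37
- 0.548 × (8/9) × 1.04 = 0.51

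Adding these men moves the middle value from 5.5 to 5.9 and the high value from 11.5 to 12.0. About 6, range about 1 to 12, is therefore a fair summary.

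Men within 30 days after exit: 0.395 × 30 = 11.8 to 0.548 × 30 = 16.4. Only those with an AE ongoing at exit could matter. The protocol gives no AE rate, and men who have exited are not clearly the active participants that section 8.5 addresses. I leave them out of the count.

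**The case against.** The strongest answer is that section 8.4 is written to work after participation ends. Its 30-day follow-up starts at study exit, and nothing limits that to a scheduled exit. A man whose participation ends because the trial closes has arguably exited, so the duty would begin by its own terms, with passive reporting after it. The SAE sentence is conditional and concerns events already identified. Section 8.4 also allows for AE and SAE submissions to local regulators, section 15 places the trial under national regulators and GCP, and section 16 has monitors check that AE/SAE reporting is complete. In that setting a general sentence about participant data is unlikely to be read as barring safety reports. Exposure is also small, at most three tablets of marketed drugs over two days.

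Much of this stands. The 30-day follow-up may survive, and the SAE conflict is weak. But the 30-day rule covers only AEs already ongoing at exit. It does not preserve the section 7.1.5 visit or provide for an event that first appears after the stop, such as a postoperative complication in a man circumcised the day before. For these, section 8.5 is the only text on data collection after an early stop, and it makes no exception.

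A reader might infer more: that the AE/SAE data on dosed men would be lost altogether, or that these men would be left without care. The protocol supports neither. Section 8.5 stops further collection and discards nothing; AEs are reviewed before later doses (7.1.3) and at the surgery visit (7.1.4). Men with symptoms of infection or major bleeding keep the section 8.2 instruction, "they will be advised to attend their local Hospital", and section 8.4 gives them telephone numbers for reporting AEs.

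**Conclusion.** The point holds as a contradiction in wording, at low severity. After an early stop, a literal section 8.5 removes the exit AE review and the recording of new AEs for men dosed or circumcised but not yet exited. What would be lost is events arising after the stop in about 6 men, range about 1 to 12. The count is an order of magnitude only: it rests on uniform accrual and an assumed gap from surgery to exit, and its upper end takes all 200 men as reaching surgery, although some replaced men leave before it.

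Whether the 30-day follow-up of ongoing AEs survives cannot be settled from the text. Nothing suggests that the sponsor meant to abandon safety follow-up; section 8.4 points the other way. The effect arises only if the trial stops early and staff let section 8.5 override section 8.4.

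**What to change.** Replace the sentence in section 8.5 with wording to this effect: early discontinuation ends enrolment, dosing and new research procedures; the exit safety visit under section 7.1.5, and AE/SAE recording, follow-up and reporting under section 8.4, continue for all men already dosed or circumcised, subject to their consent. Adding that the date of the stop does not shorten the 30-day follow-up of ongoing AEs would settle the open question about study exit. A cross-reference from section 10 would make the same rule apply to administrative closure.

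The cost is one sentence in the protocol. If the trial stops early, it also means a few safety visits that were already planned. If the trial runs to completion, it costs nothing further.

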## **9. Statistics**

### **9.1 Sample Size**

The total evaluable sample size will be 144 men; 72 in each country. For the primary comparison, data from both countries will be combined, as will the two groups where men receive the same PrEP drug and dose and differ only in timing of PrEP dose prior to circumcision. Comparisons will therefore be between 32 individuals in each treatment group. The study is not powered to detect a difference between these four treatment groups.

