**Primary objective:**

To compare the effect of different PrEP drugs (FTC-TDF and FTC-TAF), doses and timing of doses on p24 antigen level in resected foreskin tissue following HIV exposure ex vivo challenge.

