#### 4.1.1 Primary endpoint

The primary endpoint is **non-infection of foreskin tissue with HIV** (in the lab) **at 15 days** following ex vivo challenge. This is because we wish to demonstrate the potential protective effect of the drugs.

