### **Randomised trial**

A total of 144 eligible individuals (72 per country: South Africa and Uganda) will be initially approached and consented as described in Section 6.3. If eligible, they will be randomised in equal numbers to one of 9 treatment arms, each comprising a total of 16 evaluable participants, 8 per country. Four treatment arms will receive FTC-TDF (two dosing schedules, two timing schedules), four arms will receive FTC-TAF (schedules the same as for FTC-TDF) and one group will be the control group who will receive no PrEP (Figure 1, Table 1).

According to randomisation arm, circumcision will either be five or 21 hours after the last dose of PrEP has been given. Participants will take tablets at each clinic site under directly observed therapy (DOT).

Participants in the control arm will have their circumcision soon after randomisation, they will not have to wait for five hours. At the appropriate time after dosing, all other participants receiving PrEP will undergo VMMC. Their foreskins will be collected, and transferred to the local lab within two hours of circumcision. At the lab, foreskins will be processed and used for the explant HIV-

infection models. Local scientists trained by Imperial College staff from the UK will conduct experiments. Protection from HIV infection will be determined by ex vivo challenge using wild type HIV virus on freshly resected foreskins. Participants who do not take their full course of treatment, or choose to delay circumcision will be deemed to be un-evaluable and will be replaced. We will randomise a maximum of 100 consenting men to obtain 72 evaluable participants.

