[figure not shown]

Figure 1. Flow diagram of participant and foreskin journey for primary analysis (oral PrEP only). Numbers in the black boxes indicate the randomisation groups - there are nine, with each man allocated to exactly one group, with each group equally likely. This figure shows recruitment from both sites; recruitment will be split equally between South Africa (n=72) and Uganda (n=72). Numbers in green boxes refer to analysis groups. The main comparison will be between groups A-D. Group X, men who do not receive PrEP, will be used as a comparison and to ensure that the ex-vivo challenge model is successful.

Figure 2. Flow diagram of participant and foreskin journey for oral PrEP, in vitro drug exposure and ex vivo HIV challenge.

[figure not shown]

Figure 2. Flow diagram of participant and foreskin journey for oral PrEP, in vitro drug exposure and ex vivo HIV challenge. The Analysis Group Identifiers in Stage 2 comprise three components: A letter indicating the Stage 1 group; a number (5 or 21) indicating the interval between last oral PrEP dose and circumcision; and an item indicating in vitro dosing (where 0=no dose). The exceptions are the group of men who did not receive oral PrEP (Group X): these groups do not include the middle component.

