### **9.2 Analysis**

Only men who provided a foreskin sample will be included in analysis. Men who withdraw prior to circumcision will be replaced (see section 6.5). Primary groups for comparison will be men who received the same PrEP drug and dose, with no post-exposure drug, as indicated in Figure 1 (Groups A, B, C, D), pooled across the two sites. This means that data from men who received the same PrEP drug and dose, but differed in time between last dose and circumcision, will be

combined into a single group for analysis. If there is a cause to suspect that one of the timings was not effective (i.e. that the timing fell outside the effective window of the treatment regimen) then the groups will also be analysed according to randomisation groups (2-9).

Analyses will be descriptive. The primary analysis will use the result from a p24 antigen assay; p24 antigen level at day 15 after ex vivo HIV exposure; slope of p24 antigen level (day 3 to day 15) and area under the curve (day 3 to day 15).

To evaluate in vitro dosing FTC-TDF and FTC-TAF, analysis will be within randomisation groups - that is, men who received the same oral PrEP dosing. The results from foreskin tissue exposed to in vitro drug will be compared to tissue which was not exposed within an individual. All analysis will be descriptive

only; we will report results in each group, and 95% confidence intervals.

The analysis plan for estimating the pharmacodynamic dose-response curves will follow previously described methodology. The dose-response relationships between percentage protection and time since drug initiation and drug discontinuation following steady state will be generated for each drug. In addition, the relationship between pharmacokinetic parameters (concentrations of drug in rectal fluid, foreskin and plasma), pharmacodynamic outcomes, cellular activation and microbiome will be evaluated.

All demographic (age, height, weight, BMI, ethnic origin, etc.), clinical (physical examination, medical history, concomitant diseases) characteristics and survey responses will be tabulated and analysed descriptively by country.

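### Timing of doses is part of the primary objective, but the primary comparison pools 5 h and 21 h and separates them only on an undefined trigger

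*Protocol*

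**What the plan says.** All references are to the protocol.

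- **Objective.** The synopsis and section 4.1 give the primary objective as "To compare the effect of different PrEP drugs (FTC-TDF and FTC-TAF), doses and timing of doses on p24 antigen level".
- **Design.** Under Randomised trial in section 4.2, men are "randomised in equal numbers to one of 9 treatment arms, each comprising a total of 16 evaluable participants, 8 per country". Table 1 shows arms 2-9 as two drugs, two dose regimens and two intervals to surgery (5 h and 21 h), fully crossed. Arm 1 receives no PrEP.
- **Pooling.** Section 9.1 combines the countries for the primary comparison, "as will the two groups where men receive the same PrEP drug and dose and differ only in timing of PrEP dose prior to circumcision". This leaves groups A, B, C and D with 32 men each. Section 9.2 repeats this, and the Figure 1 legend states: "The main comparison will be between groups A-D".
- **Separate timings.** Section 9.2 adds an analysis by randomisation groups 2-9 on one condition: "If there is a cause to suspect that one of the timings was not effective". It does not say what counts as cause, which data would show it, or who decides.
- **Control.** Section 4.1.1 explains the choice of endpoint: "This is because we wish to demonstrate the potential protective effect of the drugs". The Figure 1 legend gives group X two roles, as a comparison and as a check on the challenge model. Section 9.2 names only A-D as primary groups.
- **Nature of the analysis.** Section 9.2 calls it descriptive, and section 9.1 disclaims power for differences between the four groups.

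**The concern.** Timing is one of three factors in the primary objective and is randomised in every regimen, yet the primary comparison averages over it. If a regimen works at only one interval, its pooled figure hides this. Schedule is part of the trial's overall aim, so this is a result the trial was set up to find.

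The fallback does not repair the gap. Whether the timings are split depends on a suspicion that the results themselves may raise, with no rule fixed in advance. Section 7.3 says the laboratories cannot be blinded to arm, and section 7.4 plans interim analyses at 30% and 60% of recruitment. A timing difference could then be reported where it is striking and left out where it is not, and a reader could not tell which had happened.

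A related, smaller gap concerns group X. Non-infection after PrEP shows protection only relative to untreated tissue, and section 9.2 does not state that contrast.

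**Working it through.** **1. The plan's own figures.** "The total evaluable sample size will be 144 men; 72 in each country": 9 arms x 16 = 144 and 9 x 8 = 72. Two timings x 16 = 32 per pooled group, and four groups x 32 = 128 treated men. All reproduce. The protocol states no effect size, infection rate or alpha, so there is no power figure to reproduce.

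**2. What pooling does.** With 16 men at each timing, the pooled proportion is the simple mean of the two. The rates below are assumed.

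| 5 h | 21 h | Pooled |
|---|---|---|
| 90% | 40% | (90 + 40)/2 = 65% |
| 65% | 65% | (65 + 65)/2 = 65% |
| 90% | 50% | (90 + 50)/2 = 70% |
| 70% | 70% | (70 + 70)/2 = 70% |

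Rows 1 and 2 give the same pooled figure, as do rows 3 and 4. No comparison among A, B, C and D can tell them apart.

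**3. What the same men could show about timing.** Arms 2, 4, 6 and 8 are at 5 h (4 x 16 = 64); arms 3, 5, 7 and 9 are at 21 h (64). Within one drug, or within one dose regimen, the contrast is 32 v 32. Within one drug-dose regimen it is 16 v 16. The approximate 95% half-width for a difference is 1.96 x sqrt(p(1-p)(1/n1 + 1/n2)), in percentage points:

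| Contrast | p = 50% | p = 70% | p = 90% |
|---|---|---|---|
| 64 v 64 | 17.3 | 15.9 | 10.4 |
| 32 v 32 | 24.5 | 22.5 | 14.7 |
| 16 v 16 | 34.6 | 31.8 | 20.8 |

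For 90% against 40%, a 50-point difference, the half-width is 1.96 x sqrt((0.9 x 0.1 + 0.4 x 0.6)/n). This is 14.1 points at n = 64 per side and 28.1 at n = 16 per side. A difference that large would show even within one regimen; a moderate one would need the 64 v 64 contrast. The normal approximation is rough at 16 men.

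**4. Contrasts with group X (16 men), at p = 50%.**

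- One of A-D against X (32 v 16): 1.96 x sqrt(0.25 x (1/32 + 1/16)) = 30.0 points.
- One timing over all regimens against X (64 v 16): 1.96 x sqrt(0.25 x (1/64 + 1/16)) = 27.4 points.
- One arm against X (16 v 16): 34.6 points.

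These are wide, but informative if the effect is large.

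**5. Whether other parts of section 9.2 cover timing.** Section 9.2 plans curves of protection for each drug against time since initiation and since discontinuation. From Table 1, time since the first dose is 5 h or 21 h in the single-dose arms, and 24 + 5 = 29 h or 24 + 21 = 45 h in the two-dose arms. On that axis, dose regimen and interval are mixed. The in vitro analysis runs within randomised arms and reports each group, so untreated-tissue results by arm may appear there as comparators. Neither part states 5 h against 21 h as a comparison.

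**The case against.** The case for the plan is substantial, and most of it stands.

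- **Drug and dose.** A reader might infer that the plan cannot answer its primary objective at all. It can for two of the three factors. Groups A-D form a drug-by-dose 2x2.
- **Use of the factorial layout.** A reader might infer that A-D are compared only in pairs and that the factorial layout is wasted. The text does not say pairwise, and 64 v 64 contrasts for drug (A+B v C+D) and dose (A+C v B+D) are not ruled out. Making them the main analysis instead of A-D would be a trade-off: they also average over timing and over one further factor, and so could hide interactions.
- **The control.** A reader might infer that the control is ignored, or that the untreated infection rate rests on site validation alone. The Figure 1 legend uses X as a comparison, there are 16 concurrent untreated men, and section 7.4 rechecks assay validity during recruitment. The primary objective names no contrast with no PrEP. What remains is an omission in section 9.2.
- **Error rates.** The analysis is descriptive and no alpha is set, so the trigger inflates no stated type I error. The harm is selective reporting.
- **Timing elsewhere.** The curves are unconditional, and the arm-level analysis would be added to the pooled one rather than replace it. Section 13 limits accumulating results by arm to the IDMC. These points soften the concern, but do not make timing a stated comparison.
- **The SAP.** It is not at hand and may define the trigger or list contrasts. But the pooling and the condition stand in the protocol, so an SAP that always reported timing would depart from it.

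**Conclusion.** Wrong as written: the primary objective includes timing, while the primary comparison removes it and restores it only on an undefined condition. The mismatch follows from the protocol's own text and needs no assumed rates. Those rates (90%, 40% and so on) only illustrate that a regimen effective at one interval and a regimen moderately effective at both can give the same pooled figure.

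In size, the plan forgoes a stated timing contrast of 64 v 64 men, with a half-width of about 10 to 17 points for non-infection between 90% and 50%. Its only stated route to the timings in the primary comparison is a conditional analysis at 16 men per arm.

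The finding does not extend to drug and dose, does not show that X goes unused, and does not rest on lack of power, since the trial claims none.

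**What to change.** In sections 9.1 and 9.2:

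1. Delete the condition on suspecting one timing, and always report arms 2-9 with 95% confidence intervals.
2. State 5 h against 21 h as a main descriptive contrast, overall (64 v 64) and by drug and dose.
3. State the difference of each of A-D, and of each timing, from group X with its 95% confidence interval, as the estimate of protection. This carries the role given to X in the Figure 1 legend into the analysis section.
4. Keep the A-D comparison. Marginal contrasts for drug and dose (64 v 64) may be added, but should not replace it.

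Only analysis wording changes: no added men, visits or assays, and the sample size stays at 144. The downside is more estimates to present, with wide intervals at 16 men per arm. The change is best made before results by arm are available.
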